Safety outcomes include analysis of between-group differences in:Air quality samples from an infection control perspective (A TSI optical particle sizer device will be used to collect data on fugitive aerosol emissions during nebulisation, and throughout randomly selected 24-h periods in intubated and non-intubated patients, and in control and treatment arm patients.) This will be a descriptive analysis of air quality information in a selected number of patients.Number of patients transfused red blood cells to day 10Volume of red blood cells transfused to day 10Number who record major bleeding to day 10‘Major bleeding’ is defined as bleeding that results in death and/or bleeding that is symptomatic and occurs in a critical area or organ (intra-cranial, intra-spinal, intra-ocular, retroperitoneal, intra-articular or intramuscular with compartment syndrome) and/or bleeding that results in a fall in haemoglobin of 20g/l or more, or results in transfusion of two or more units of whole blood or red cells [13]Number of patients who record clinically relevant non-major bleeding as defined by the International Society on Thrombosis and Haemostasis [14]Number who record a diagnosis of heparin-induced thrombocytopenia (HIT)Number who record other adverse events and reactionsAdverse events will be assessed systematically with patient and chart reviews on a daily basis, with all clinical events reviewed and assessed by the investigator, and adverse events recorded and reported appropriately. AEs will be classified by organ system

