#### Sample size {14}

This is a phase 1b/2a study aiming to evaluate the effect of nebulised unfractionated heparin on procoagulant markers and the safety of nebulised heparin in patients receiving advanced respiratory support for COVID-19 lung disease. This has not been studied previously, and as such, data does not exist to power the study accurately to assess clinical outcomes. We have chosen to base our power analysis on some of our own in house data for d-dimer levels in COVID patients who required ICU care (12 patients) and those who did not (26 patients) (unpublished data from very early in the pandemic).

Based on an estimation that nebulised heparin may reduce the d-dimer levels in ICU patients (mean = 944.8ng/ml [SD = 485.3]) to those experienced in ward patients (mean = 436.5ng/ml [SD = 604.0]), with an alpha level of 0.05 and a power of 90% to detect a type II error, 19 patients per group would be required. Increasing the number by 1 per group to allow for potential dropout gives a sample size of 20 patients per arm of the study, with a total of 40 patients to be enrolled. The safety profile of administering nebulised heparin to invasively ventilated patients with COVID-19 will be a co-primary outcome. The study is not powered for analysis of the co-primary endpoint of serious adverse events due to insufficient pre-existing data in this population. Power analysis is based only on the outcome of d-dimer as described above.

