### Assignment of interventions: allocation

#### Sequence generation {16a}

Allocation will be carried out after consent is confirmed, via a central, secure web randomisation process hosted by the contract research organisation (CRO). Allocation will be in a one-to-one ratio, with variable block size randomisation. The code for the randomisation process is embedded in the eCRF. The Programme R was used to generate the randomisation sequence.

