### Statistical methods

#### Statistical methods for primary and secondary outcomes {20a}

Demographic and baseline characteristics of the study population will be summarised using appropriate graphical and numerical summaries for each treatment group and by site. The primary analysis approach will be an intention-to-treat analysis, with a per-protocol analysis also being carried out. The per-protocol analysis will include any patient who received any dose of the study drug in the treatment group and any patient who underwent data collection for at least one time point in the standard care group. A safety analysis set will be included including all recruited patients. For effectiveness analysis, we will use the 2-sample *t*-tests (or suitable non-parametric test depending on data distribution) for the between-group difference in d-dimer levels and generalised linear (or non-linear as appropriate) mixed effects models for the analysis of longitudinal data, using appropriate link functions depending on the type of outcome variable. This analysis will be used to compare the treatment effect, while adjusting for patient characteristics (e.g. Horowitz index of lung function (P/F ratio), Sequential Organ Failure Assessment (SOFA) score, body mass index (BMI), sex and age) as appropriate for all primary and secondary efficacy outcomes. A Cox proportional hazards model will be used to model time to event responses. Generalised linear models will be used for the analysis of safety outcomes. Primary and secondary outcome data will be suitable for meta-analysis to further assess clinically relevant outcomes. Interval estimates (95% confidence intervals) for the treatment effect will be reported accordingly.

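### Generalised linear models are the only named method for comparing safety between arms; for the rare binary events, 20 per arm makes a zero cell likely, and the default ratio interval and p value then carry no information

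*Protocol article*

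**What the plan says.** In the Protocol article, section {20a}, the whole provision for comparing the arms on safety is "Generalised linear models will be used for the analysis of safety outcomes". The section closes by promising 95% confidence intervals for the treatment effect. It names no link, no type of test and no alternative for sparse data. The d-dimer comparison in the same paragraph does have an alternative: "or suitable non-parametric test depending on data distribution".

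The safety list in Outcomes {12} consists largely of numbers of patients. It includes "Number who record a diagnosis of heparin-induced thrombocytopenia (HIT"), major bleeding to day 10 and clinically relevant non-major bleeding. Air quality is on the list too, but is to be analysed descriptively.

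Sample size {14} "gives a sample size of 20 patients per arm of the study, with a total of 40 patients to be enrolled". On the safety population, {20a} says: "A safety analysis set will be included including all recruited patients".

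**The concern.** A generalised linear model with a logit or log link estimates a ratio. If one arm has no events, the maximum-likelihood ratio is infinite (or zero, if the empty arm is the heparin arm). The standard error that software reports is then an artefact of where the iterations stopped, and the Wald p value sits near 1 whatever the count in the other arm. If both arms are empty, there is no ratio to estimate.

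The documents make safety an objective, and the occurrence of serious adverse events (SAEs) is a co-primary outcome. Sample size {14} concedes that the study is not powered for it. The between-arm estimates and intervals are therefore the main thing the safety comparison can offer. Events confined to the heparin arm are the pattern a safety reader most wants described well, and the default output of a ratio-scale model describes it worst.

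**Working it through.** **Inputs.** Arms of 20 (Sample size {14}) with 1:1 allocation (Sequence generation {16a}). The safety set is all recruited patients, so about 20 v 20. The article states no figure for safety, so there is none to reproduce. It gives no event rates, so the rates below are assumptions.

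**Step 1: how likely is a zero cell?** With true rate *p* in both arms, P(one given arm has no events) = *q* = (1 − *p*)^20, and P(at least one arm has none) = 1 − (1 − *q*)².

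| Assumed rate | *q* | At least one arm empty | Exactly one empty | Both empty |
|---|---|---|---|---|
| 1% | 0.818 | 97% | 30% | 67% |
| 2% | 0.668 | 89% | 44% | 45% |
| 5% | 0.358 | 59% | 46% | 13% |
| 10% | 0.122 | 23% | 21% | 1.5% |
| 20% | 0.012 | 2% | 2% | about 0 |

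With a true excess on heparin, P(control 0, heparin at least 1) = (1 − *p*c)^20 × [1 − (1 − *p*h)^20]. This is 59% for 2% v 10%, 66% for 2% v 20%, and 36% for 5% v 25%.

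**Step 2: what does the model report for 5/20 v 0/20?**

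- Logistic GLM, default output: log odds ratio 22.47, SE 17,768, Wald p = 0.999. The 95% interval on the log scale is 22.47 ± 1.96 × 17,768, or about ± 34,800.
- Likelihood-ratio test from the same model: maximised log-likelihood 5 ln 0.25 + 15 ln 0.75 = −11.25; null 5 ln 0.125 + 35 ln 0.875 = −15.07; statistic 2 × 3.82 = 7.65, p = 0.006. The profile-likelihood lower limit for the odds ratio is 2.60, with no finite upper limit.
- Score test: 0.25 / √(0.125 × 0.875 × 2/20) = 2.39, p = 0.017.
- Fisher's exact test, two-sided: 2 × C(20,5)/C(40,5) = 2 × 15,504/658,008 = 0.047.
- Newcombe interval: Wilson limits are 0.112 to 0.469 for 5/20 and 0 to 0.161 for 0/20. Lower limit 0.25 − √[(0.25 − 0.112)² + 0.161²] = 0.038; upper limit 0.469. The risk difference is 25 points, 95% CI 4 to 47.

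**Step 3: does the answer depend on what the plan leaves open?**

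| Heparin v control | Wald p | Likelihood-ratio p | Score p | Fisher p | Newcombe 95% CI (points) |
|---|---|---|---|---|---|
| 3/20 v 0/20 | 0.999 | 0.036 | 0.072 | 0.231 | −4 to 36 |
| 4/20 v 0/20 | 0.999 | 0.014 | 0.035 | 0.106 | −0.1 to 42 |
| 5/20 v 0/20 | 0.999 | 0.006 | 0.017 | 0.047 | 4 to 47 |
| 6/20 v 0/20 | 0.999 | 0.002 | 0.008 | 0.020 | 8 to 52 |

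Wald, likelihood-ratio and score inference all fall within the stated method. At 3 v 0 they give p values from 0.036 to 0.999 on the same data.

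**The case against.** The strongest reply is that the article names a class of models and does not fix a logit link or Wald inference. Other members of the class work. The likelihood-ratio and score tests above are usable. An identity-link binomial model gives a finite 25-point risk difference with a simple interval of 0.25 ± 1.96 × √(0.25 × 0.75/20), about 6 to 44 points. Fisher's test is also more conservative than the likelihood-ratio and score tests (4 v 0: 0.106 against 0.014 and 0.035), although the likelihood-ratio p is itself approximate at such counts. All of this stands. It rules out saying that the model reports nothing, but it also confirms that the stated plan permits very different answers.

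A second reply is that link and test are detail usually left to a full protocol or analysis plan, and section {31c} calls the article a summary protocol. This has some weight. Against it, the article's title says that it includes the statistical analysis plan, and the method it does name, with its usual output, suits these outcomes poorly.

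A reader might also infer more than the documents support:

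- **That a safety signal would be hidden.** The outcomes are numbers of patients, so 5 v 0 would be visible. The Medical Monitor and the data safety monitoring committee review SAEs.
- **That every safety outcome is affected.** Air quality is descriptive only.
- **That the SAE co-primary fails.** No SAE rate is given, but if SAEs are common, as is plausible in intensive care, an empty arm is unlikely (2% at a 20% rate).
- **That red-cell volume is affected because most values would be zero.** Nothing in the article shows that, and volume has no zero-cell failure.

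**Conclusion.** The concern holds for the rare binary safety outcomes: HIT, major bleeding and clinically relevant non-major bleeding. If their true rates are about 5% or lower, an arm of 20 with no events is more likely than not to occur (59% at 5%, 89% at 2%); at 10% the chance is 23%. In that case a ratio-scale model has no finite estimate, its default Wald interval and p value carry no information, and no finite two-sided ratio interval exists.

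The conclusion rests on two assumptions: the event rates, which the article does not give, and a logit or log link with default output, which it does not exclude. The defect is confined to the planned interval and p value for these outcomes, and to the choice of inference being left open in an open-label trial. It does not make the events invisible, and it is no evidence that the SAE co-primary analysis fails.

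**What to change.** Replace the safety sentence in {20a} with a rule along these lines:

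- For each binary safety outcome, the main summary is the count per arm and the risk difference with a Newcombe or Miettinen-Nurminen score 95% confidence interval.
- If a p value is wanted, one small-sample test is named in advance: an exact unconditional test, or Fisher's with a note that it is conservative.
- Ratio-scale generalised linear models are a supplement, used only where both arms have events.

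The change takes a few lines and needs no new data. The cost is that sparse outcomes get no covariate-adjusted estimate. That is a small loss: 40 patients could support little adjustment of a rare event, and {20a} describes adjustment for patient characteristics only in connection with the efficacy models.

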#### Interim analyses {21b}

There is no plan to carry out an interim analysis as the primary outcome is not a clinical outcome, and the numbers recruited are small.

#### Methods for additional analyses (e.g. subgroup analyses) {20b}

Results will be presented as per-protocol and intention-to-treat analysis groups. Results will also be presented for ventilated at enrollment and non-ventilated at enrollment subgroups, although due to the sample size the numbers in each group will be small.

#### Methods in analysis to handle protocol non-adherence and any statistical methods to handle missing data {20c}

All participants who are enrolled will be included in the analysis. Any participants who withdraw and wish to have their data withdrawn will not be included. Analysis will be carried out using the intention-to-treat principle where patient’s data will be analysed as members of the group they were randomised to, irrespective of their compliance with the treatment as specified in the protocol. A separate per-protocol analysis will be carried out including all patients who complied with the protocol in terms of exposure to planed treatment, availability of measurements and absence of major protocol deviations. Any deviation(s) from the original statistical plan will be described and justified in the final report. [An analysis of all missing data will be carried out to identify the likely missing data mechanism (e.g. missing completely at random, missing at random, and missing not at random) and to investigate the reasons for missingness as a useful outcome for the corresponding subsequent definitive trial.] Multiple imputation using chain equations will be used to handle missing data (due to outcome values missing in some visits for some of the participants) in the primary and secondary outcome analysis.

#### Plans to give access to the full protocol, participant-level data and statistical code {31c}

The full protocol is available on application to the investigators, with the summary protocol published here. The statistical code will be published as an addendum to the results paper after completion of the study. Participant-level data will be maintained confidentially, with some clinical outcome data feeding into the CHARTER and INHALE-HEP international meta-trials [15, 16]. Reasonable requests for access to the data from other investigators will be considered by the investigators, taking into account General Data Protection Regulation (GDPR) compliance.

### Oversight and monitoring

#### Composition of the coordinating centre and trial steering committee {5d}

The Health Research Board Clinical Research Facility (HRB-CRFG) Galway will be the coordinating centre, taking overall responsibility for the conduct of the trial. All members of the investigator team and research group will have appropriate GDPR and ICH GCP training, which will be documented in a delegation log. Regular meetings between each site and the coordinating centre, facilitated by the CRO, will allow communication of progress, highlighting of adverse reactions and discussion of technical issues. A detailed plan of sponsor oversight with regular site audit has been devised.

#### Composition of the data monitoring committee, its role and reporting structure {21a}

An independent international Data Safety Monitoring Committee (DSMC) will oversee the conduct of the trial and verify the correct implementation of the clinical trial design. Just as with a traditional trial design, the role of the DSMC is to ensure the design is implemented with integrity, that the original design remains scientifically and ethically appropriate in light of the accumulating data and any external information, and to protect research participants from avoidable risk. The DSMC for this trial will include expertise in critical care, biostatistics and clinical trials.

The responsibilities of the DSMC are to advise on all matters related to the safety of subjects enrolled in this study, the integrity of trial data and conclusions and the appropriateness of continued trial conduct.

The aims of the DSMC include:To identify any trends, such as increases in un/expected events, and take appropriate actionTo seek additional advice or information from investigators where requiredTo evaluate the risk of the trial continuing and take appropriate action where necessary

The researchers will provide the DSMC with an interim report of adverse events and early results. The DSMC will also undertake a review of enrolments and withdrawals according to the DSMC Charter, to ensure adequate study safety, and minimal risk to participants. Where necessary, the DSMC will make recommendations for corrective action which may include early termination, suspension or modification of a trial, or changes in consent processes. However, the final decision will rest with the sponsor.

### Adverse event reporting and harms {22}

#### Procedures for recording adverse events

Reportable adverse events and reactions will be communicated by site investigators to the chief investigator. In general, this will occur in writing within no more than 3 days of the site investigator becoming aware of the event. The management committee will assess all safety reports received from investigators.

All adverse events occurring during the trial that are observed by the investigator or reported by the participant will be recorded on the eCRF, whether or not attributed to trial medication.

The following information will be recorded: description, date of onset and end date, severity, assessment of relatedness to trial medication, other suspect drugs or devices and action taken. Follow-up information should be provided as necessary. Only non-serious adverse events which are considered related to the investigational medicinal product will be recorded routinely on the adverse event eCRF from the time of informed consent (or enrolment into the study) up to 96 h after the last dose of study drug has been received. All adverse events meeting ‘serious’ criteria should be recorded on the SAEs CRF as per Section below.

#### Procedures for recording and reporting SAEs

All SAEs must be reported on the SAE reporting form to the sponsor within 24 h of the study team becoming aware of the event.

The sponsor will perform an initial check of the report, request any additional information and ensure it is reviewed by the Medical Monitor on a weekly basis.

Adverse events meeting the definition of SAEs must be reported using the SAE report form located in the investigator site file. All adverse events meeting ‘serious’ criteria occurring in each patient should be reported from the time of informed consent (or enrolment into the study) up to 90 days after the last dose of study drug has been received. All SAE information must also be recorded on the SAE form within the eCRF. Additional and further requested information (follow-up or corrections to the original case) may be captured within the SAE form and eCRF. Follow-up/new information is required within the same reporting timeline, i.e. within 24 h of the study team becoming aware of the new information.

SAEs will also be reviewed by the DSMC, in accordance with their Charter.

Sponsor responsibilities:

The sponsor, National University of Ireland Galway (NUIG), will delegate appropriate adverse event reporting for the study according to the applicable regulatory guidelines.

NUIG will submit local suspected unexpected serious adverse reactions (SUSARs) on an expedited basis to the local regulatory authority and other Competent Authorities involved, concerned Ethics Committees, all participating investigators and the DSMC. NUIG sends annual Development Safety Update Reports to the concerned regulatory authority and Ethics Committee. Investigators will be informed of SUSARs.

For fatal and life-threatening SUSARS, this will be done no later than 7 calendar days after the sponsor is first aware of the reaction. Any additional relevant information will be reported within 8 calendar days of the initial report. All other SUSARs will be reported within 15 calendar days.

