**Discussion:**

This trial aims to provide evidence of potential therapeutic benefit while establishing safety of nebulised heparin in the management of ARDS associated with SARs-CoV-2 infection.

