#### Outcomes {12}

The co-primary outcomes are:A between-group difference in d-dimer levels over time, assessed by measurement of area under the curve (AUC) on days 1, 3, 5 and 10A between-group difference in the occurrence of serious adverse events (SAEs) as listed in the safety analysis

Secondary efficacy outcomes include analysis of between-group differences in:Oxygenation index (OI) = (FiO_2_ × M_PAW_)/PaO_2_ will be recorded every 6 hPulmonary compliance will be recorded every 6 h up to day 10 in invasively ventilated patientsDynamic pulmonary compliance is measured automatically on our ventilators (Puritan Bennett and Servo I) and recorded on the ICU Clinical Information System), measured as ∆V/∆PInflammatory and coagulation markersIL-1β, IL-6, IL-8, IL-10, soluble tumour necrosis factor receptor 1, C-reactive protein, procalcitonin, ferritin, fibrinogen and lactate dehydrogenase LDH will be assessedAUC measurement for these inflammatory and coagulation markers on days 1, 3, 5 and 10Ratio of IL-1β/IL-10 and IL-6/IL-10Time to separation from invasive ventilation to day 28, where non-survivors to day 28 are treated as though not separated from invasive ventilation, measured in daysNumber tracheotomised to day 28 (*N*)Time to separation from the ICU to day 28, where non-survivors to day 28 are treated as though not separated from invasive care measured in daysSurvival to day 28, survival to day 60 and survival to hospital discharge, censored at day 60

Additional outcomes include:Time to separation from invasive ventilation to day 28, among survivorsNumber treated with neuromuscular blockers instituted after enrolment to day 10Any administration of neuromuscular blocking drugs will be recordedNumber treated with prone positioning instituted after enrolment to day 10Number treated with extra-corporeal membrane oxygenation instituted after enrolment to day 10Time to separation from the ICU to day 28, among survivors, measured in daysNumber residing at home or in a community setting at day 60Number residing at home or in a community setting at day 60, among survivors

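### Adverse event windows end at the last dose of study drug, which controls never receive, and the rules for recording non-serious events contradict each other

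*Protocol article*

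**What the plan says.** All references are to the Protocol article.

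- **What is compared.** Outcomes {12} names as a co-primary the "between-group difference in the occurrence of serious adverse events (SAEs) as listed in the safety analysis", with no time horizon. The safety outcomes in the same section, also framed as between-group differences, include a count of patients with any other adverse event or reaction.
- **SAE capture.** Procedures for recording and reporting SAEs: "All adverse events meeting ‘serious’ criteria occurring in each patient should be reported from the time of informed consent" or enrolment, "up to 90 days after the last dose of study drug has been received".
- **Non-serious capture.** Procedures for recording adverse events first says that all adverse events seen by the investigator or reported by the participant "will be recorded on the eCRF, whether or not attributed to trial medication". It then says: "Only non-serious adverse events which are considered related to the investigational medicinal product will be recorded routinely on the adverse event eCRF", from consent or enrolment "up to 96 h after the last dose of study drug has been received".
- **Exposure.** Intervention description {11a} gives the control arm standard care without nebulised heparin. There is no placebo. In the heparin arm, dosing runs to day 10 at most and may stop earlier under Table 2.
- **Blinding and analysis set.** Who will be blinded {17a} leaves patient-facing staff unblinded. Statistical methods {20a} puts all recruited patients in the safety set.
- **Follow-up.** The last scheduled data collection in Participant timeline {13} is day 60.

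**The concern.** A between-group comparison of event occurrence needs the same observation period and the same recording rule in both arms. Here the period ends relative to an event, the last dose, that cannot happen in the control arm, and no substitute anchor such as randomisation is given. The same gap affects any heparin-arm patient who is never dosed but remains in the safety set.

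For non-serious events there is a second problem. If recording depends on being judged related to the product, the control arm is close to empty by definition, and the judgement is made with the arm known. Both are rules for data collection, so analysis cannot recover what was never entered for controls.

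**Working it through.** The plan states no SAE rate and no figure to reproduce. The check sets the rules side by side, works out the windows, and then illustrates the possible size of the effect.

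**Step 1: windows in the heparin arm.** Inputs: last dose between day 0 and day 10 ({11a}, Table 2); 90 days for SAEs; 96 h = 4 days for non-serious events.

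- SAE window closes between 0 + 90 = day 90 and 10 + 90 = day 100.
- Non-serious window closes between 0 + 4 = day 4 and 10 + 4 = day 14.
- Against day 60, the SAE window runs 90 − 60 = 30 to 100 − 60 = 40 days past the last scheduled collection.

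The end also moves with events after randomisation, because Table 2 withholds dosing for reasons such as bleeding or coming off advanced respiratory support.

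**Step 2: windows in the control arm.** With no dose there is no last dose. Both windows are undefined. The text does not show them to be shorter or longer.

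**Step 3: which filter applies to which events.**

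| Events | Anchored to last dose | Relatedness filter |
|---|---|---|
| SAEs (co-primary) | Yes, 90 days | None; reported in each patient |
| Non-serious AEs, first sentence | No end stated | None |
| Non-serious AEs, later sentence | Yes, 96 h | Related to product only |
| Transfusion, major bleeding | No; to day 10 in both arms | None stated |

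The second and third rows cannot both be followed. Under the third, a never-exposed patient can hardly have a qualifying event. Clinically relevant non-major bleeding and heparin-induced thrombocytopenia carry no relatedness condition in Outcomes {12}, but no window is given there either. Which recording rule covers them is not stated.

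**Step 4: illustration for SAEs.** Assumptions, none of them from the document: the same constant hazard h in both arms, and a heparin window of 100 days. For a 100-day risk p, h = −ln(1 − p)/100, and the control risk over w days is 1 − exp(−h·w). For p = 0.50, h = 0.00693 per day; at w = 60 the control risk is 1 − exp(−0.416) = 34.0%, so the spurious difference is 50.0 − 34.0 = 16.0 points.

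| Control window | Control risk (p = 30%) | Control risk (p = 50%) | Control risk (p = 70%) | Spurious difference, points |
|---|---|---|---|---|
| 28 days | 9.5% | 17.6% | 28.6% | 20.5, 32.4, 41.4 |
| 60 days | 19.3% | 34.0% | 51.4% | 10.7, 16.0, 18.6 |
| 90 days | 27.5% | 46.4% | 66.2% | 2.5, 3.6, 3.8 |
| 100 days | 30% | 50% | 70% | 0 |

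The 90-day row also shows that the day 90 to 100 spread within the heparin arm matters little.

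**The case against.** The strongest reply concerns the co-primary. SAE reporting has no relatedness filter and is to be done in each patient, so controls are covered and the open-label judgement of relatedness does not decide which SAEs count. Nothing in the article stops control SAE capture at day 60 or sooner. If sites follow controls for about 90 to 100 days, or if day 60 is the practical limit in both arms, the artefact is small or absent. If controls were followed longer than treated patients, it would reverse. A constant hazard from acute intensive care illness to day 100 is also a strong assumption. All of this stands. A reader might infer that the SAE comparison is biased against heparin, or cannot be interpreted at all; the document does not support either reading.

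Day 60 against day 100 is not in itself a contradiction: Plans for assessment and collection of outcomes {18a} draws adverse event data from health records, other providers and the patient or proxy with no day-60 limit. It does mean that the last weeks of SAE capture have no scheduled collection behind them.

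The article summarises a full protocol and mentions eCRF completion instructions, and either might give controls an anchor. That could supply the missing end point. It would not remove the conflict between the two recording sentences, which are both in the published text.

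A reader might also add that the safety comparison lacks power or a success rule, or object to the Abstract's phrase "while establishing safety of nebulised heparin". Sample size {14} openly says the SAE outcome is unpowered, a decision rule is commonly left to the analysis plan, and the phrase is a matter of wording. None of these bears on event capture.

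**Conclusion.** The point holds in two parts of different strength.

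1. **Non-serious events.** The article contradicts itself, and under the restrictive sentence the between-group comparison is biased by construction, with a control count near zero whatever the true effect. This needs no assumption beyond that sentence being the one sites follow.
2. **SAEs.** The co-primary has no defined observation period in the control arm, and in the heparin arm the period ends 30 to 40 days after the last scheduled collection. Bias is possible but not shown. Under the stated assumptions it ranges from nil, with equal windows, through 11 to 19 points for a 60-day control window, to 21 to 41 points for 28 days.

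Major bleeding and transfusion are counted to day 10 in both arms, so the dose-anchored windows do not affect them.

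**What to change.** - For the between-group analyses, count SAEs and other adverse events over one fixed window from randomisation, the same length in both arms, whether or not any study drug was given, and consistent with scheduled follow-up. SAEs to day 60 would be one such choice.
- Keep any longer post-dose reporting for pharmacovigilance, stated separately and outside the comparison.
- Reconcile the two sentences in Procedures for recording adverse events so that every event compared between arms is recorded identically regardless of relatedness. Otherwise, drop the between-group comparison of non-serious events and report related events in the heparin arm descriptively.
- State which rule and window apply to clinically relevant non-major bleeding and heparin-induced thrombocytopenia.

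The cost is a change to the protocol and the eCRF instructions, plus some extra adverse event entry for controls, for whom Outcomes {12} already describes daily patient and chart review. SAEs after the fixed window would be left out of the comparison. Trial status expected recruitment to finish in Spring 2022, so if sites have been using the restrictive sentence, control events would have to be retrieved from charts, or that comparison given up.
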